Currently, there is no consensus about which music works best for which patient. Previous research investigated the psychophysiological effect of self-chosen music, highlighting the importance of individual preferences [20]. While research on pain (management) is increasingly sensitive for socio-cultural differences [21,22], research on MIA notably lacks consideration for socio-cultural background characteristics such as level of education, age or ethnicity. Sociological studies have established that these characteristics – cultural capital as a trait of level of education most specifically – act as key factors contributing to musical taste differentiation [[23], [24], [25], [26], [27]] and music perception [28,29]. Moreover, these factors affect musical taste patterns, which in turn are closely aligned with listening experience and social identity, in which musical taste plays a significant role as well [30,31]. For example, people who have enjoyed higher education levels are typically much more inclined to like ‘highbrow’ music such as classical or jazz [24,26], which also prescribe different behaviors – e.g. sitting, contemplation, not singing along – during listening and concerts than less ‘legitimate’ music preferences such as rap, schlager or heavy metal [32]. As a consequence, these socio-cultural background characteristics can potentially affect MIA [26,27], which is why this should be considered when investigating the therapeutic effects of music on pain.

This study aims to investigate whether the effect of (preferred) music on pain endurance remains consistent across different socio-cultural backgrounds. With this study, we will combine knowledge from different disciplines by integrating sociological methods into medical research, which could provide new perspectives on music as medicine. The MOSART study adopts a cross-over design, wherein every participant will undergo three distinct interventions in a randomized sequence: 1) self-chosen music, 2) researcher-chosen music, and 3) a neutral spoken-word podcast as a control condition. Following each intervention, participants will be subjected to increasing electric stimuli to assess changes in pain endurance.

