#### Pain endurance

2.4.1

The primary outcome of this study is pain endurance, quantified in amperage, through increasing electric stimuli administered at the end of each intervention (self-chosen music, researcher-chosen music, and control). The electric stimuli will be administrated by the STMISOLA (Biopac Systems Inc. Goleta, CA, USA). Two electrodes will be attached to the index finger of the non-dominant hand. Administration of the electrical pulses with a frequency of 100 Hz will start when the participants press a button with the other, dominant hand. When this button is pressed, electric pulses with a current increase rate of 0.5 mA/s will be administered up to a maximum of 30 mA for safety reasons.

When the experiment starts and the participant is connected to the device, the sensation threshold will be tested. At the end of each intervention, while the participants are still listening to music or the podcast, the pain endurance will be tested. Standardized instructions will be used, instructing participants to tolerate the electric pain stimuli as long as possible. Each measurement will be repeated three times, and the average amperages will be registered.

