### Data management and statistical analysis

2.5

Data will be managed using Castor EDC (Ciwit B·V., Amsterdam), a certified data capture tool that includes skips, validation checks and an audit trail. This study will look at the influence of (preferred) music on MIA across different socio-cultural backgrounds (through an explorative approach. For normally distributed data, we plan to utilize a linear mixed model to analyze both the primary outcome (pain endurance) and secondary outcomes (pain intensity and unpleasantness, HRV, SAM, STAI-6). In the fixed-effects part of the model the following effects will be included: intervention, position within randomization sequence, age, TRAIT anxiety, level of education, economic capital (income), participants' cultural capital, parents’ cultural capital and ethnicity. Interaction terms such as intervention and position within randomization sequence will eventually be included using F and likelihood ratio test. In the random-effects structure we will incorporate random intercepts and a random effect of the time point of sequence. Because of the continuous measurement of HRV during each intervention the time point (within each intervention) will be included as fixed and random effect. This way, we will consider the period effect and potential carry-over effects of the cross-over study design. In the event of not normally distributed data a Friedman test will be performed instead. Moreover, subgroup analyses excluding participants with maximal pain endurance during all three interventions and non-adherence to the protocol will be performed. Data analysis will be performed using R version 4.0 or higher.

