#### Relation between pain endurance, music and socio-cultural background

3.2.1

Previous research indicates a crucial role of socio-cultural background (level of education and cultural capital) in music taste formation and music perception [[23], [24], [25], [26], [27], [28]]. Thus, while it is clear that people with different backgrounds have different musical tastes, it is not clear to what extent the impact of music on pain endurance depends on these features. We hypothesize two contrasting possibilities.

First, we hypothesize that the impact of music largely depends on the degree to which it aligns with personal taste, as previous research indicates [18,19]. People will then respond most to the type of music they actually appreciate and benefit less from music that leaves them indifferent or even annoys them. In this scenario, music that fits participants’ taste will enhance pain endurance more than non-preferred music. If personal taste is indeed important, irrespective of the exact taste, we expect its effect to be similar across groups with different socio-cultural backgrounds. Our first hypothesis is therefore that the positive impact of self-chosen, preferred music on MIA is consistent for all participants.

Second and in contrast, if researcher-chosen music has a universal beneficial impact, then people's (socially differentiated) taste should not affect the degree to which music enhances pain endurance. In other words: the impact of taste should be absent, irrespective of one's socio-cultural background, demonstrating that some types of music are simply more effective in providing MIA than others. In this scenario, our second hypothesis is then that the positive impact of researcher-chosen music on MIA is consistent for all participants, independent of their socio-cultural backgrounds.

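### If the data are judged non-normal, a Friedman test replaces the mixed model, leaving no stated analysis of whether the music effect is consistent across backgrounds

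*Protocol article*

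**What the plan says.** Section 2.5 of the protocol article makes the main model conditional: "For normally distributed data, we plan to utilize a linear mixed model to analyze both the primary outcome (pain endurance) and secondary outcomes". The fixed effects begin with "intervention, position within randomization sequence, age, TRAIT anxiety, level of education, economic capital (income), participants' cultural capital" and go on to parental cultural capital and ethnicity. On interactions it says: "Interaction terms such as intervention and position within randomization sequence will eventually be included using F and likelihood ratio test". After describing the random effects and the handling of HRV time points, it adds: "This way, we will consider the period effect and potential carry-over effects of the cross-over study design". The alternative follows at once: "In the event of not normally distributed data a Friedman test will be performed instead". No transformation, rank-based model, censored model or between-stratum comparison is named for that case.

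The Background gives the aim: "This study aims to investigate whether the effect of (preferred) music on pain endurance remains consistent across different socio-cultural backgrounds". Section 3.2.1 frames both hypotheses as consistency. The first is that "the positive impact of self-chosen, preferred music on MIA is consistent for all participants"; the second says the same of researcher-chosen music. Section 2.3.1 stratifies by education so that the three categories can be compared.

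On the primary outcome, section 2.4.1 says the current is "administered up to a maximum of 30 mA for safety reasons". Section 2.5 also foresees people who reach the ceiling in all three conditions, since it plans an analysis without them.

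**The concern.** The aim is a question about effect modification: does the music effect differ by background? The fallback has no place for background. If it is used, the only planned result is one global test of whether the three conditions differ, in ranks. The socio-cultural variables, the period effect and the carry-over check go with the model that is replaced.

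The trigger is also loosely placed. It refers to the distribution of the data, whereas a mixed model relies on approximately normal residuals and random effects. Raw amperage pooled over conditions and strata can look non-normal while the residuals are acceptable. The outcomes make the question a practical one: endurance stops at 30 mA, the NRS has 11 points, and SAM and STAI-6 are bounded scores.

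**Working it through.** **Inputs from the article.** 84 participants, 28 per education stratum; d = 0.4; two-sided 5%; 90% power (section 2.2). Three conditions in randomised Latin-square order (section 2.1). A ramp of 0.5 mA/s to 30 mA, so the ceiling is reached after 30/0.5 = 60 s (section 2.4.1). The ICC and the dropout rate are not given.

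**1. The plan's own figure.** For a paired comparison, n = 2(1 − ICC)(1.960 + 1.282)²/d².
- ICC 0.5: 2 × 0.5 × 10.51/0.16 = 65.7, so 66. The exact paired t calculation gives 68, and 68/(1 − 0.19) = 84.
- ICC 0.42: 2 × 0.58 × 10.51/0.16 = 76.2, so 77. The exact calculation gives 79, and 79/0.95 = 83.2, so 84.
- Over ICC 0.2 to 0.7 the exact n before dropout runs from 108 to 42.

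So 84 is attainable but cannot be confirmed. The point below does not depend on it.

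**2. What the Friedman test uses.** With n participants, k conditions and rank sums R_j,

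Q = 12/[nk(k + 1)] × ΣR_j² − 3n(k + 1).

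For n = 84 and k = 3 this is Q = ΣR_j²/84 − 1008. Only three rank sums enter. Shuffling the education labels among the 84 participants leaves Q unchanged, so Q cannot say whether the effect differs by education. The same holds for income, cultural capital and ethnicity. Position varies within a participant, but it has no term either.

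**3. Planned needs against the two analyses.**

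| Need | Mixed model as printed | Friedman |
|---|---|---|
| Overall intervention effect | yes | yes, in ranks |
| Estimate in mA | yes | no |
| Education and other background variables | main effects listed; interaction with intervention not written out | none |
| Position, carry-over | position as a term; its interaction with intervention possible | none |
| Participants with a missing condition | can contribute | dropped |
| HRV time points within an intervention | fixed and random effect | cannot be used |

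**4. Illustrative simulation.** All of the following are assumptions, not figures from the article: within-person correlation 0.5, six sequences, effects in SD units, 1,500 runs per scenario. Friedman was compared with within-subject F tests for intervention (adjusted for position) and intervention × education. For complete balanced data these match a random-intercept mixed model. Errors are normal unless stated.

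- A: both kinds of music +0.4 SD over the podcast in every stratum.
- B: as A, but self-chosen music +1.0/+0.4/−0.2 in the three strata (mean 0.4).
- C: self-chosen music +0.6/0/−0.6 (mean 0), researcher-chosen 0.
- Trend: a period effect of 0/0.5/1.0 SD over the three positions.

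| Scenario | Friedman | Intervention F | Intervention × education F |
|---|---|---|---|
| A | 90% | 97% | 5% |
| B | 87% | 96% | 99% |
| C | 4% | 3% | 99% |
| A, skewed errors | 99% | 96% | 5% |
| A, with trend | 72% | 97% | 5% |
| No effect, with trend | 1% | 5% | 5% |
| B, outcome capped at +0.5 SD | 78% | 81% | 90% |

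Friedman hardly separates A from B, the two states the trial wants to tell apart, and it misses C. Under the trend it becomes conservative; it does not produce excess false positives.

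Two further checks. Separate Friedman tests in each stratum of 28 rejected in only 42% to 44% of runs in A, and they would not test a difference between strata. A Kruskal-Wallis test across strata on the self-chosen minus podcast difference rejected in 5% of runs in A, 97% in B and 98% in C. A rank method for the question therefore exists, but the article does not plan one.

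**The case against.** **The data could still answer the question.** A reader might infer that a non-normal result makes the research question unanswerable. It does not: the rank comparison of within-person differences above works well. What is missing is a stated analysis, not information. This objection stands.

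**The printed mixed model does not clearly test consistency either.** Education and the other background variables are listed as main effects, and the only interaction given as an example is intervention with position. It would be wrong to say that the switch alone removes a fully specified heterogeneity analysis. The 99% in the table belongs to a model with the interaction added. This limits the harm due to the fallback. It does not rescue the fallback, which has no background term at all.

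**Order is randomised.** A reader might infer that an uncorrected period effect would bias the comparison. With balanced sequences it does not; it costs power and the carry-over check.

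**The overall test is sound.** With skewed errors Friedman did slightly better than the F test (99% against 96%). This stands, and it is why the test deserves a place as a sensitivity analysis.

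**The trigger may be rare.** The article gives no endurance distribution and no proportion at 30 mA, and the recorded value averages three measurements. Foreseeing ceiling cases does not show that they are common, so a claim that the switch is likely to occur is unsupported for the primary outcome.

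**A fuller analysis plan may say more, and the socio-cultural analysis is called exploratory (sections 2.5 and 3.3).** How normality is judged may well be set out elsewhere, and the exploratory label lowers the confirmatory stakes. But the replacement rule is printed as definite, and an exploratory aim still needs a method that can address it.

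**Conclusion.** The point holds in a limited form. As written, whenever the data are judged non-normal, no analysis of consistency across backgrounds is specified for any outcome, and the period and carry-over handling credited to the mixed model disappears. That conclusion is structural and needs no assumption.

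The sizes are illustrative and rest on the assumed correlation, effects and period trend. Friedman rejects in 90% against 87% of runs for a consistent and a strongly inconsistent effect. Its power falls from 90% to 72% under a steep period trend, while a model with position stays at 97%. The overall three-condition comparison remains testable. Non-normality is plausible given the 30 mA cap and the bounded scales, but its probability cannot be quantified from the article. This is a defect to repair before analysis; it does not invalidate the design or the data.

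**What to change.** Remove the replacement rule and state one analysis:

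- Keep the linear mixed model with its planned covariates whatever the distribution of the raw data, and write out an intervention × education term. The other background variables can stay exploratory.
- Judge model residuals, not raw values.
- Pre-specify inference robust to non-normality for the same contrasts, for example a bootstrap that resamples whole participants. Report it in every case, so that it does not become a second data-driven switch.
- For endurance, add a mixed model right-censored at 30 mA as a pre-specified sensitivity analysis. Because the recorded value is an average of three measurements, say how an average that includes a capped reading is treated.
- Optionally, add an ordinal mixed model for NRS and SAM.
- Keep Friedman only as a sensitivity analysis of the overall intervention effect.

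Two tempting shortcuts fall short. A log transformation does not repair censoring at the cap. Permuting the randomised orders does not directly test intervention × education, because education is not randomised.

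The cost is revised wording and some extra R code. Sample size and procedures do not change. The revision should be dated before the outcome data are analysed.

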### Ethical approval and trial status

2.6

The study protocol received ethical approval from the Medical Ethical Review Committee of the Erasmus Medical Center in Rotterdam (registration number MEC-2023-0253) on July 31, 2023, before the start of the study. This study will be conducted according to the principles of the Declaration of Helsinki (64th WMA General Assembly, Fortaleza, Brazil, October 2013) and in accordance with the Medical Research Involving Human Subjects Act. The trial is registered with the National Institute of Health (www.clinicaltrials.gov, ID: NCT06008951). All participants will be asked for written informed consent and will receive financial compensation for their time investment.

This study protocol (version 2.1, October 24th, 2023) follow the SPIRIT (Standard Protocol Items: Recommendations for Interventional Trials) guideline [66] and the CONSORT (Consolidated Standards of Reporting Trials) guidelines for non-pharmacological treatments [67].

## Discussion

3

### Bridging sociological and medical research

3.1

This study will be the first experimental trial that integrates sociological theories and methods into medical research on MIA, which could provide new perspectives on music as medicine. As a result of this collaboration, we aim to assess the effects of a range of relevant socio-cultural background indicators on MIA. Sociological research indicates, among other findings, that music preference correlates with socio-cultural background characteristics, including gender, ethnicity, cultural capital, and economic status. Furthermore, the chosen music can influence individuals' behavior, actions, and emotions [26,27]. As pain is defined as an “unpleasant sensory and emotional experience,” it is expected that different music preferences will influence emotions and thereby also the experience of pain [53]. Moreover, it seems probable that music influences pain through neurobiological processes, such as the activation of the parasympathetic nervous system and the release of endogenous neurotransmitters. These effects may also depend on music perception and socio-cultural background characteristics [4,50].

The MOSART study was designed as a collaboration between the medical research group ‘Music as Medicine’ of the Erasmus Medical Center Rotterdam and the ‘Rotterdam Popular Music Studies’ group of the Erasmus University Rotterdam. This sociological research group focuses on the reception of music in relation to social background characteristics. The medical research group specializes in investigating the physiological and health-related effects of music, including MIA and its influence on the autonomic nervous system, as measured with HRV. We believe in providing a unique perspective that enhances our comprehension of how socio-cultural background contributes to MIA.

### General aspects and considerations about the study

3.2

#### Relation between pain endurance, music and socio-cultural background

3.2.1

Previous research indicates a crucial role of socio-cultural background (level of education and cultural capital) in music taste formation and music perception [[23], [24], [25], [26], [27], [28]]. Thus, while it is clear that people with different backgrounds have different musical tastes, it is not clear to what extent the impact of music on pain endurance depends on these features. We hypothesize two contrasting possibilities.

First, we hypothesize that the impact of music largely depends on the degree to which it aligns with personal taste, as previous research indicates [18,19]. People will then respond most to the type of music they actually appreciate and benefit less from music that leaves them indifferent or even annoys them. In this scenario, music that fits participants’ taste will enhance pain endurance more than non-preferred music. If personal taste is indeed important, irrespective of the exact taste, we expect its effect to be similar across groups with different socio-cultural backgrounds. Our first hypothesis is therefore that the positive impact of self-chosen, preferred music on MIA is consistent for all participants.

Second and in contrast, if researcher-chosen music has a universal beneficial impact, then people's (socially differentiated) taste should not affect the degree to which music enhances pain endurance. In other words: the impact of taste should be absent, irrespective of one's socio-cultural background, demonstrating that some types of music are simply more effective in providing MIA than others. In this scenario, our second hypothesis is then that the positive impact of researcher-chosen music on MIA is consistent for all participants, independent of their socio-cultural backgrounds.

#### Conceptual basis of time periods used within study design

3.2.2

The length of the (music) listening periods were based on previous clinical and experimental studies [5,33,68]. Although clinical trials show especially high discrepancies in the length of music listening, ranging from 5 to 120 min, the most frequent listening durations last between 15 and 30 min [16,69]. Therefore, we chose to incorporate a 20-min period for all three interventions (self-chosen music, researcher-chosen music and control condition).

The choice of a 20-min wash-out period was grounded in the pharmacokinetics of potential key neurochemicals implicated in MIA. Given the incomplete understanding of the mechanisms underlying MIA, we aimed for the wash-out period to be strategically positioned relative to the half-lives of potential key neurochemicals. Studies have highlighted the involvement of neurotransmitters such as dopamine, beta-endorphin and oxytocin in modulating pain perception in MIA [[70], [71], [72]]. The half-life times of these specific neurotransmitters have a broad range from 1 min to 1.5 h, but predominantly last from a couple of minutes to 20 min [[73], [74], [75]]. By allowing a 20-min wash-out period between the interventions in this study, we aim to minimize carryover effects. This rationale aligns with the principles of crossover study design, facilitating the accurate assessment of treatment effects while controlling for potential confounders and randomization sequence. Additionally, the choice of a 20-min duration aims to balance the need for an adequate wash-out period with considerations for volunteer comfort and study feasibility.

### Challenges of the study

3.3

In the MOSART study, we aim to ensure a diverse study population with varied socio-cultural backgrounds. This emphasis is crucial because inclusive medical practice demands that we focus on more diverse social backgrounds, distinct from the typically prevalent highly educated Western study cohorts that have been overrepresented in prior experimental research on MIA [13]. Therefore, we are opting to employ stratification based on education level, recognizing it as one of the most important indicators for socio-cultural background. According to earlier sociological research experience, it can be challenging to include volunteers with lesser education levels in experimental studies in the Netherlands. Therefore, we are planning to expand communication strategies to reach more potential participants, especially from less- and medium-educated strata.

Another challenge can be found in the multidisciplinary aspect of this study. This study is based on collaboration among the interdisciplinary research group with researchers from the departments of anesthesiology, surgery and neuroscience, and sociology. A challenge in this collaboration is that the research methods can differ, for instance in study design and sample size. For example, to combine a manageable sample size that aligns with sociological aspects (higher sample sizes) with relatively time-demanding inclusions common in medical research (lower sample sizes), we are choosing an exploratory approach toward analyzing sociological variables. Moreover, by only including female participants, we aim to establish a more homogenous study population so that drawing valid conclusions about the effects of the socio-cultural background indicators remains feasible. This is particularly important as gender differences – especially the gender of researchers and participants – are strongly linked to pain perception [38,[76], [77], [78]]. Therefore, only female participants and researchers will be involved in this study. Finally, given that pain and music preference are multidimensional concepts, we contend that a comprehensive understanding of our research question can only be achieved by combining various disciplinary insights that are integral to the design of this research protocol.

